**Instructions for SAE recording and reporting**

The study site will make copies of the blank initial and follow-up SAE report forms as needed. The site will retain originals of all information faxed to PPD Development in the Investigator Site File. Any Serious Adverse Event (SAE) must be **reported immediately** by telephone to the Medical Affairs/Pharmacovigilance Department at PPD Development at **[contact]**. A written description of any SAE must be sent to PPD Development by **facsimile** (**[contact]**) **within 24 hours** of its occurrence. The site personnel will refer to the protocol for further clarification.

**Note:** **If there is any question as to whether an event should be reported, call PPD to discuss the event in question at [contact].**

## 3.8. Drug levels and pharmacokinetic assessments

No drug levels other than study drug will be assessed. Blood samples for pharmacokinetic analysis of prosaptide will be drawn from subjects at **designated** study sites only. It is anticipated that approximately 100 study subjects will participate in the pharmacokinetic testing.

Pharmacokinetic analysis will be performed according to a predetermined randomization schedule at Visits 4, 6 and 7. Subjects will be randomized to one of three sampling sequences (ABC, BCA, CAB) and will have samples drawn at the following schedule as indicated under Table 3-6. Subjects participating in the pharmacokinetic analysis will take their dose of study medication for the day at the clinic visit. The **dose at Visit 4** should be a vial from the **Week 1** carton. The **dose at Visit 6** should be a vial from **Week 4** carton, and the **dose at Visit 7** should be a vial from the **Week 6** carton.

###### Table 3-6: Blood sample collection schedule for pharmacokinetic analysis

| **Schedule** | **Time** |
| --- | --- |
| A | predose, **1** hour and **3** hours postdose |
| B | predose, **1.5** hours and **4** hours postdose |
| C | predose, **0.5** hours and **2** hours postdose |
| Note: All subjects will be required to have blood samples taken within ±15 minutes of the specified time following drug dosing. Further details are given under Appendix 2, Section 1.2-AP2. | |

The study coordinator at each site will document the exact time of dose administration as well as the exact timing of the blood sample on the CRF. All subjects will be required to have blood samples taken within 15 minutes of the specified time following dosing administration for pharmacokinetic plasma analysis.

Statistical methods for the pharmacokinetic analysis are given under Section 6.1.7.

# 4. Protocol amendments and other changes in study conduct

## 4.1. Protocol amendments

Any changes to the protocol will be made in the form of an amendment. Based on the results of the interim futility analysis, it is possible that one or more treatment arms may be dropped from the study. If this occurs, a protocol amendment will be issued to all sites delineating this change.

## 4.2. Other changes in study conduct

Changes in study conduct are not permitted. Any unforeseen changes in study conduct will be recorded in the clinical study report.

# 5. Data management

## Data collection

Investigators must enter the subject information required by the protocol onto the study sponsor’s case report forms (CRFs) that are printed on 3-part, non-carbon required (NCR) paper. The original and one copy of the CRFs will be forwarded to the CRF desk of the sponsor’s representative (PPD). One copy will be retained at the investigational site and is subject to the required document retention policy (see Appendix 1 Section 4. Document retention). Once the CRFs are received by PPD, their receipt is recorded, the original copy is placed in the study files and the NCR copy is forwarded to the responsible data management staff for processing.

During their regular visits, a study monitor will review the CRFs for completeness and accuracy, and instruct site personnel to make any required corrections or additions to CRFs that are at the site. Study representative (the study monitor) initiated data queries will be utilized for any corrections required to CRFs that have already been forwarded to PPD at the time of the study monitor’s visit.

Additional information is given under Appendix 2, Section 2.3.3-AP2 of this protocol.

## Database management and quality control

Data items from the CRFs are entered into the study database using appropriate methodology to ensure that the CRFs are accurately represented.

Information entered into the database is subjected to systematic logic and consistency checking routines. Obvious errors will be corrected by the appropriate data management personnel in accordance with the data handling and entry guidelines for the study. Findings from the electronic process defined above are reviewed by qualified data management or clinical personnel, after which electronically generated query forms are returned to the investigational site for resolution. Each site is expected to respond promptly to data queries. **The investigator** **must sign and date all responses to queries from CRF pages requiring an investigator signature**. Other query responses may be signed by either the investigator or a designee. After signature, the original query form should be sent to the sponsor’s representative (PPD) for database update and a copy filed with the subject’s CRF. Quality control edit checks of key safety and efficacy data in the database will be made regularly throughout the duration of the study.

Concomitant medications entered into the database will be coded using the WHO Drug Dictionary which classifies according to therapeutic/pharmacological class. Coexistent diseases and adverse events will be coded using MedDRA.

Laboratory samples including blood samples for prosaptide antibody determinations will be processed through the central laboratory facility (ICON Laboratories), and the results will be sent electronically to PPD with copies to the site. Prosaptide antibody and plasma drug levels will remain blinded until the conclusion of the study.

# 6. Statistical methods

## 6.1. Statistical methods

This is a double-blind, randomized, placebo controlled study with five dose groups (0, 2, 4, 8, 16 mg/per day). The primary efficacy endpoint is the change of the Gracely pain average score during Week 6 from the Week 0 baseline level (Week 0 minus Week 6 score). The primary objective is to select at least one dose group which is significantly better than the placebo with respect to this endpoint. Furthermore, the dose response relationship among these four groups will be examined.

Due to the slow enrollment, the protocol is amended to restrict further enrollment in the lowest dose arm (2 mg). It is expected that a sufficient number of subjects will have been treated at 2 mg before the amendment is fully implemented. An inferential statistical comparison between the 2 mg and placebo groups will still be carried out if there is a sufficient statistical power to detect a clinically meaningful treatment difference. Regardless, all dose groups will be used to characterize safety and dose response.

The study will be stratified with respect to SNAP (+ or -). For each stratum, a random treatment allocation rule will be utilized so that the balance among these five dose groups (four dose groups after the amendment) within each center will be maintained during the study.

It is planned that the data from all centers that participate in this protocol will be combined, so that an adequate number of subjects will be available for analysis. The results from each center will also be presented individually. In addition, it is planned that the data from both SNAP positive and SNAP negative subjects will be combined in the final analysis if there is no interaction between treatment effects and SNAP status.

The significance for all statistical tests will be reported at the p=0.05 level, and all tests will be 2-sided. Each dose group will be compared to the placebo group and a 95% confidence interval for each comparison will be provided. Because this is a phase 2 study, no adjustments for multiplicity will be made.

Since subjects receiving active treatment during the 42-day double-blind period will receive placebo injections for 2 weeks at visit 7 and those receiving placebo will be crossed over to receive prosaptide 4 mg, within group comparisons between visits 7 and 8 can be performed to examine the treatment effects due to the cross over. Change from visit 7 by dose group for the following parameters will be summarized: Gracely pain scale, McGill pain questionnaire, global physician impression, and safety laboratories.

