### 3.3.2. Treatment assignment

Subjects will be stratified by center and SNAP status and randomized to receive prosaptide 2, 4, 8 or 16 mg or look-alike placebo every 24 hours for 6 weeks. All blocks of 5 kits that have had one or more kits assigned must be used until the supply is exhausted in order to maintain the blind. A mechanism for removing the 2 mg kit from a block with five intact, unassigned study kits will be implemented by the Sponsor in a manner that preserves the blind. All subsequent shipments of study drug will consist of four study kits: 4, 8 or 16 mg prosaptide or placebo. Study kits will be distributed in numerical order, with each subject receiving the next kit for his or her SNAP group available at the site.

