### 6.1.5. Efficacy evaluation

The primary analysis will be an intent-to-treat analysis. The standard 95% confidence intervals for treatment differences between each dose and placebo groups will be constructed for the primary efficacy endpoint. Since the study is stratified with respect to the SNAP status, separate confidence intervals will be constructed for each stratum. If there is no interaction between treatment efficacy and SNAP, the two intervals will be combined across the strata to have a global confidence interval for evaluating each dose effect. If the safety profiles for the four dose groups are similar, the recommended dose will be the one with the best efficacy (largest lower bound of the confidence interval).

Similar analyses will be repeated for the secondary efficacy endpoints. For the secondary endpoint analyses, the weekly pain scores will be calculated for each subject. In order to take advantage of such repeated measurements in the analysis, a 95% confidence interval of the difference between a dose group and the placebo will be constructed at each week. These intervals will be combined using the technique by Wei and Johnson25 to obtain a single more informative confidence interval for the treatment difference over the entire study period.

Subjects with greater than 0.35-unit pain improvement on the 13-point Gracely scale at Week 6 will be classified as treatment successes. Treatment group comparisons will be carried out using the Chi-square test and Fisher’s exact test. The standard confidence interval of the difference of the weekly success rates between a dose group and placebo will be constructed. For this dichotomized response, a single interval estimate across the entire study period will be computed using the Wei and Johnson technique.

In addition, an analysis of covariance (ANCOVA) which adjusts for the differences in baseline Gracely pain scale will be conducted for both primary and secondary efficacy endpoints. Primary and secondary efficacy analyses will also be repeated adjusting for other factors that may affect the outcome. Candidate predictive factors are SNAP amplitude at baseline, type of sensory neuropathy (DSP versus ATN), CD4 counts, plasma viral load, age, body mass index (BMI), duration of disease, and background antiretroviral therapy.

Additional efficacy analyses will include per protocol analyses. The previously described statistical approach will be repeated for this population.

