# Appendix 2: Procedures and instructions

## 2.1-AP2. Labeling, packaging, storage, and return of clinical supplies

### 2.1.1-AP2. Packaging of clinical supplies

#### Study drug (prosaptide or placebo)

Clinical supplies for 855 subjects (randomization numbers 90001-90885) will be provided. One or more blocks of five subjects will initially be sent to each individual center in validated, insulated containers with cold packs. Additional supplies will be packaged and held by Fisher Clinical Services under frozen conditions. Fisher will remove the 2 mg kit from the remaining unshipped blocks, so that each block will contain only four kits (4, 8 or 16 mg prosaptide, and placebo). Each subject will be assigned a kit containing eight cartons of study medication. There will be nine single use vials per carton.

Prosaptide is stable for at least 12 months when stored at -15° C. Prosaptide is stored frozen at -5o C to -20o C until shipment to the investigative centers. Shipment is performed by validated shipping containers that allow the study medication to remain below 8° C during transport.

INVESTIGATIVE SITES MUST STORE THE MEDICATION IN A SECURE FREEZER AT -15oC ±5oC. TWELVE ICE PACKS WILL BE INCLUDED IN THE SHIPMENT. THESE MUST BE TAKEN FROM THE SHIPPER AND STORED FROZEN AT THE SITE FOR DISTRIBUTING TO SUBJECTS WHEN DISPENSING THE FIRST 2 WEEKS OF STUDY SUPPLIES. THE STUDY SUBJECTS WILL BE INSTRUCTED THAT THE MEDICATION MUST BE STORED IN A REFRIGERATOR AT ALL TIMES AND WILL BE PROVIDED WITH A SMALL COOLER AND 2 COLD PACKS EACH FOR TRANSPORTING THE STUDY DRUG TO AND FROM THE CLINICAL CENTERS.

At 5°C, prosaptide is stable for up to 3 months. It is stable at room temperature for short periods of time. If left at room temperature for more than **24 hours**, **the sponsor’s representative (PPD) should be contacted for further instructions.**

Prosaptide or look-alike placebo is **dosed subcutaneously into the abdomen on a once daily basis**. One mL of prosaptide should be given at each administration regardless of dosage strength. Each vial is intended for a single subject dose, and any excess left in the vial after dosing should **not be used for further dosing.** Specific instructions for self-administration are provided in Appendix 3.

Look-like placebo will be supplied as sterile phosphate buffered saline with 3% mannitol, pH 6.8. Placebo is packed in 2 mL sterile glass vials with Teflon-faced stoppers and flip-off caps.

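### Randomization is stratified by center and SNAP, but no stated treatment comparison includes center, so the planned intervals are mildly too wide if centers differ

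*Protocol*

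**What the plan says.** On allocation, section 3.3.2 states "Subjects will be stratified by center and SNAP status and randomized", and kits are used in order, with "each subject receiving the next kit for his or her SNAP group available at the site". Section 6.1 describes the rule, applied separately by SNAP: "a random treatment allocation rule will be utilized so that the balance among these five dose groups (four dose groups after the amendment) within each" (the sentence goes on to name the center as the unit of balance). Blocks held five kits at first. Under Amendment 2, Appendix 2 (section 2.1.1-AP2) says "Fisher will remove the 2 mg kit from the remaining unshipped blocks, so that each block will contain only four kits".

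On analysis, section 6.1 says "It is planned that the data from all centers that participate in this protocol will be combined", to have enough subjects, and adds "The results from each center will also be presented individually". Section 6.1.5 defines the primary analysis as a standard 95% confidence interval for each dose against placebo and explains where SNAP comes in: "Since the study is stratified with respect to the SNAP status, separate confidence intervals will be constructed for each stratum". The two SNAP intervals are combined if treatment and SNAP do not interact. The ANCOVA adjusts for baseline Gracely score. The candidate factors for further adjusted analyses are SNAP amplitude, neuropathy type, CD4 count, viral load, age, body mass index, disease duration and antiretroviral therapy. Center is not among them.

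**The concern.** Section 6.1.5 brings SNAP into the primary interval because the randomization is stratified by it. The same reason applies to center, the other stratification factor, but is not followed there.

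Blocking within center spreads each center's subjects across the arms, so differences between centers largely cancel out of each dose-placebo comparison. A standard error computed without center does not reflect this: it treats the between-center variation as random error. The interval is then wider than the design warrants, and precision gained by the randomization is not used. That matters somewhat in a trial that amended its design because of slow enrollment. The results by center do not recover it: 355 subjects at about 30 centers is about 12 per center, or 2 to 3 per arm.

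**Working it through.** **Inputs from the protocol.** SD of change 0.35, difference 0.17, two-sided alpha 0.05, 70 evaluable per group, half-width 0.12 (section 6.3); 10% dropout (section 3); 355 subjects and about 30 centers (synopsis); blocks of 5, later 4 (section 3.3.2 and Appendix 2). **Assumed:** the between-center share of variance (ICC), for which the protocol gives no value; range 0.02 to 0.20.

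**Step 1: reproduce the plan's figures, with no center term.**

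- Half-width = 1.96 × 0.35 × √(2/70) = 0.116, stated as 0.12.
- Power: 0.17 / (0.35 × √(2/70)) = 2.87; 2.87 − 1.96 = 0.91, which gives 82%, against a stated minimum of 80%.
- Enrollment: 280/0.9 + 45 = 356, against 355.

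All three agree with section 6.3.

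**Step 2: variance with and without credit for blocking.** The planned standard error uses

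V_planned = σ² (1/n1 + 1/n0).

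Under center blocking the same estimator has variance

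V_true = (1 − ICC) σ² (1/n1 + 1/n0) + ICC σ² Σ_c (n1c/n1 − n0c/n0)²,

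where n1c and n0c are the numbers on dose and on placebo in center c. The sum measures how unevenly the two arms are spread over centers. Relative to (1/n1 + 1/n0) it is about 1 without blocking and 0 with perfect balance.

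In 2,000 simulated allocations (311 subjects in four arms, 30 unequal centers × 2 SNAP strata, blocks of 4, 10% dropout) this ratio averaged 0.238. Blocking thus removes about three quarters of the chance imbalance, even with small center-by-SNAP cells. Hence

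V_true / V_planned = 1 − 0.762 × ICC.

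For example, at ICC 0.10 this is 0.924, with square root 0.961. The planned interval is 1/0.961 − 1 = 4.0% wider than the same estimator warrants, and its coverage is 2Φ(1.96/0.961) − 1 = 95.9%.

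**Step 3: compare with a random center effect.** A model over all arms with treatment, SNAP and a random center effect also uses the remaining within-center information. Ratios are taken before rounding.

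| Assumed ICC | Planned half-width | Warranted, same estimator | Random center model | Planned wider than random center model by | Coverage of planned interval |
|---|---|---|---|---|---|
| 0.02 | 0.1160 | 0.1151 | 0.1151 | 0.8% | 95.2% |
| 0.05 | 0.1160 | 0.1138 | 0.1136 | 2.1% | 95.4% |
| 0.10 | 0.1160 | 0.1115 | 0.1109 | 4.7% | 95.9% |
| 0.20 | 0.1160 | 0.1068 | 0.1049 | 10.6% | 96.7% |

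Squaring the width ratios gives the extra subjects needed to match the random center model without a center term: about 4% (1.021²), 10% (1.047²) and 22% (1.106²) at ICC 0.05, 0.10 and 0.20.

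**Step 4: sensitivity.** Five arms in blocks of 5 with 355 subjects gave excess widths of 0.8%, 2.1%, 4.7% and 10.7%. Fifteen centers with 390 subjects gave 0.9%, 2.4%, 5.1% and 11.4%.

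**Step 5: which form of center term.** In simulated trials with 30 fixed center effects, power against the SNAP-only analysis was 79.3% v 81.4% at ICC 0, 82.1% v 81.4% at 0.05, 84.1% v 82.0% at 0.10 and 88.9% v 85.2% at 0.20. Fixed effects can therefore cost about 2 points if centers do not differ. A random center effect showed no such loss at ICC 0: power under the two analyses was 81.5% and 81.3%.

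**The case against.** The strongest case on the other side is that nothing the protocol promises fails. Without center, the plan delivers its power and its half-width. The error is on the safe side, and at an ICC of 0.05 or less the excess width is about 2% or less. Whether center enters as fixed, random or pooled is commonly left to a statistical analysis plan, which is not shown here. The factors in section 6.1.5 are only candidates, so center is not ruled out. Section 3.1.2 gives a prognostic reason for stratifying by SNAP and none for center. All of this stands as to size. It does not remove the point, because the protocol itself fixes the primary interval, gives stratification as the reason for including SNAP, and does not carry that reason over to center.

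A reader might infer more than the documents support:

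- **That the intervals lose their 95% coverage in a way that undermines the inference.** Coverage stays at 95.2% to 95.9% for ICC up to 0.10 and reaches 96.7% only at 0.20. The departure is over-coverage, so type I error is not inflated.
- **That the dose choice is distorted.** The recommended dose is the one with the largest lower bound. The 4, 8 and 16 mg arms are planned at 70 each against the same placebo group, so a common widening lowers their bounds about equally. For a 2 mg arm of 45 the half-width is 1.96 × 0.35 × √(1/45 + 1/70) = 0.131, which is 0.015 more than 0.116. A 5% inflation moves that gap by less than 0.001.
- **That the results by center are worthless and could give way to a center effect from a model.** They are imprecise, but a center main effect says nothing about whether the treatment difference is consistent across sites.

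**Conclusion.** The point holds as a modest loss of efficiency. Randomization is stratified by center and SNAP, and every stated treatment comparison leaves center out. The planned intervals are about 1%, 2%, 5% and 11% too wide at assumed between-center shares of 2%, 5%, 10% and 20%, with coverage of about 95% to 97%. If centers do not differ, nothing is lost.

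The size depends entirely on that share, which the protocol does not give, and to a lesser degree on the simulated layout of about 30 centers, small blocks and 10% dropout. The protocol's type I error, power and half-width claims stand, and the ranking of the equal-sized arms is essentially unchanged. The change is worth making because it aligns the analysis with the randomization at almost no cost.

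**What to change.** In section 6.1.5, obtain the dose-placebo differences and their 95% confidence intervals from one linear model over all dose groups, with treatment, SNAP stratum and center as a random effect. Pooling centers below a pre-specified size is an acceptable alternative. Thirty fixed center effects are not advised, for the reason in step 5 of the working. Use the same center term in the ANCOVA and the weekly analyses. Keep the descriptive results by center in section 6.1.

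This changes analysis wording only and needs no new data or subjects. The downside is a slightly more complex model, with little gain if centers differ little.

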#### Exploratory measures

- comparison of the duration of treatment effect in the 2-week placebo crossover period (Week 7 through Week 8) among the treatment arms in subjects who were treatment successes
- comparison between the difference in number of doses of rescue medication used during the Week 0 baseline period and number used during each week of the active treatment period between 2, 4, 8, and 16 mg prosaptide and placebo
- comparison between McGill pain questionnaire differences from the Visit 4 baseline measurement and Week 7 measurements between 2, 4, 8, and 16 mg prosaptide and placebo
- comparison between global physician impression differences from the Visit 4 baseline measurement and Week 7 measurements between 2, 4, 8, and 16 mg prosaptide and placebo

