## 3.1. Overall study design

This will be a randomized, double-blind, placebo-controlled multicenter study design using four dosing levels (2, 4, 8, and 16 mg/day) to evaluate the efficacy and safety of prosaptide for the relief of neuropathic pain associated with HIV-1. An interim analysis will be performed when 200 subjects complete 6 weeks of treatment.

Subjects will be washed out of **adjuvant pain medications** including anticonvulsants, antidepressants, topical analgesics and short-acting narcotics. Long acting opioid analgesics (maintained at a constant daily dose throughout the study) will be permitted in up to 20% of screened subjects at each study site. Subjects taking long-acting narcotics must have received a constant daily dose for at least 30 days prior to Visit 1. All subjects will receive a supply of **acetaminophen 500 mg caplets** as **rescue medication**. Subjects who have intolerable pain despite rescue medication are permitted to discontinue from the study at any time.

The double-blind phase will include a 6 week active treatment phase with subjects receiving one of the 4 dosing levels of prosaptide or placebo as illustrated in Figure 3-1.

Subjects who meet entry criteria, including a pain level of Gracely 0.74 log units averaged over the 2-week period between Visit 2 and Visit 3, and have completed written informed consent will be randomized into the study. Subjects randomized after the **two part** screening phase will complete a one week baseline period, then will receive one of four active treatment or placebo for a **42-day** double-blind treatment period. This will be followed by a **2-week** double-blind **crossover period**, during which subjects previously receiving active treatment will receive placebo injections. **The group receiving placebo during the 42-day double-blind treatment period will be crossed over to receive prosaptide 4 mg for 2 weeks,** forming a modified **cross-over** design*.* The purpose of the crossover period is to assess the duration of prosaptide response after discontinuation of treatment. In addition, it increases the number of subjects who receive active treatment, enhancing the ability to assess the magnitude of the placebo response, and the secondary outcome of early pain response. It also allows all subjects the opportunity to receive active therapy at some point during the study. Study visits will occur every 2 weeks during both double-blind periods.

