## 3.3. Treatments

### 3.3.1. Investigational therapy, reference therapy and rescue medication

#### Treatment plan

The treatment plan is as follows:

- At Visit 3 (see Table 3-1 under Section 3.4, designated as “**R**” column), subjects will be randomized to one of four prosaptide doses (2 mg, 4 mg, 8 mg, or 16 mg), or look-alike placebo in a double-blind manner until all opened drug blocks with the 5 dose groups have been used. Subsequently, subjects will be randomized to one of only three prosaptide doses (4, 8 or 16 mg) or placebo in a double-blind manner (see section 3.3.2).
- At Visit 4, subjects will receive one of the dosing levels of drug or placebo (double-blind treatment phase).
- At Visit 7, subjects will be “**crossed over,**” with subjects who received active drug receiving placebo and subjects who received placebo receiving 4 mg of prosaptide (double-blind crossover phase).

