For those subjects in the prosaptide groups who were treatment successes, the mean Gracely pain scale during the crossover placebo period will be calculated. The time at which the mean Gracely pain scale returns to the baseline level will be summarized by treatment group.

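### Within-group Visit 7 to Visit 8 changes cannot isolate a crossover treatment effect; a between-arm difference in that change should carry any such statement

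*Protocol*

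**What the plan says.** Under the treatment plan in section 3.3.1, all subjects on active drug move to placebo at Visit 7 and all subjects on placebo move to prosaptide 4 mg, double-blind, for two weeks.

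For this period, section 6.1 states that "within group comparisons between visits 7 and 8 can be performed to examine the treatment effects due to the cross over". It continues: "Change from visit 7 by dose group for the following parameters will be summarized", listing the Gracely scale, the McGill questionnaire, the global physician impression and safety laboratories. It names no comparison of that change between arms.

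Section 3.1 gives the aim: "The purpose of the crossover period is to assess the duration of prosaptide response after discontinuation of treatment". It adds that the crossover puts more subjects on active treatment, "enhancing the ability to assess the magnitude of the placebo response, and the secondary outcome of early pain response".

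The one between-arm comparison planned for these weeks is an exploratory measure in section 2.4, the duration of effect "among the treatment arms in subjects who were treatment successes". Its analysis in section 6.1.5 reads: "For those subjects in the prosaptide groups who were treatment successes, the mean Gracely pain scale during the crossover placebo period will be calculated". That leaves out the placebo-to-4 mg arm.

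**The concern.** Section 6.1 names an estimator and says what it is for: the effect of the treatment switch. A change within one arm does not measure that. From Visit 7 to Visit 8, pain scores can also move because time passes, because subjects know that a switch takes place at that visit, or because scores regress. With no arm staying on its treatment, nothing inside an arm shows how large that movement is.

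Two false readings could follow without any drug effect: an early response in placebo subjects moved to 4 mg, or a loss of effect in active subjects moved to placebo. The second use named in section 3.1 has the same weakness, because the placebo-to-4 mg change has no concurrent placebo control.

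The responder summary does not fill the gap. It covers a subset chosen by outcome after randomisation, without the placebo-to-4 mg arm. Yet the trial has randomised sequences running in opposite directions over the same two weeks, and comparing their changes removes whatever shift they share.

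**Working it through.** **Inputs.** From section 6.3: 70 evaluable subjects per arm, SD of change 0.35, average placebo response 0.17, design difference 0.17, two-sided 0.05. The protocol gives no SD and no non-drug drift for Visit 7 to Visit 8. I assume an SD of 0.20 to 0.35 and a drift of 0 to 0.17. The value 0.085 is half the protocol's placebo response (0.17/2).

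**The plan's own figures.** There is none for the crossover analysis, so I checked the sample-size figures that supply the inputs. The half-width of the 95% CI between two arms is 1.96 × 0.35 × √(2/70) = 0.116, which rounds to the stated 0.12. Power at 70 per arm for a difference of 0.17 is 82%, consistent with the stated minimum of 80%. Both reproduce.

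**Within-group test, no drug effect.** SE = 0.35/√70 = 0.0418, so a mean shift above 1.96 × 0.0418 = 0.082 is significant. With drift m, the rejection probability is Φ(m/SE − 1.96) + Φ(−m/SE − 1.96):

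| Drift m | m/SE | Within-group rejection | Between-arm rejection |
|---|---|---|---|
| 0 | 0 | 5% | 4.9% |
| 0.05 | 1.20 | 22% | 4.9% |
| 0.085 | 2.03 | 53% | 4.8% |
| 0.17 | 4.06 | 98% | 5.2% |

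Using the noncentral t distribution instead gives 21.8%, 51.7% and 98.0% for the last three rows. The between-arm column is a two-sample t-test on the change, 70 per arm, in 20,000 simulated trials per row, with the same drift in both arms. A smaller SD makes the within-group test worse: at a drift of 0.05 the rate is 38% with SD 0.25 and 54% with SD 0.20.

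**What the between-arm contrast estimates.** Count improvement as positive. Suppose a true drug effect of 0.17 that is fully reached within the two weeks, with a fraction c still present at Visit 8 after stopping.

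- Placebo-to-4 mg: 0.17 + m
- 4 mg-to-placebo: −0.17(1 − c) + m
- Difference: 0.17 + 0.17(1 − c)

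The drift m cancels. The difference is 0.34 for c = 0, 0.255 for c = 0.5 and 0.17 for c = 1. Its SE is 0.35 × √(2/70) = 0.0592, which is √2 times 0.0418. Under these assumptions power is at least the 82% found above for a difference of 0.17.

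**The case against.** The strongest reply is that the protocol commits to very little. The within-group comparisons are only permitted. What is promised is a summary by dose group, which is already descriptive and shows the arms side by side. The primary and secondary endpoints end at Week 6 and are compared with placebo between arms, and the dose recommendation in section 6.1.5 rests on the primary-endpoint interval. All of this stands and keeps the severity modest. It does not remove the point, because the permission comes with a causal purpose that the comparison cannot serve.

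The drift and SD are indeed borrowed. Section 6.3 gives 0.17 and 0.35 for sizing the primary comparison, not for two weeks that follow six weeks of blinded injections. The rejection rates are therefore conditional, and at zero drift the test holds 5%.

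The between-arm contrast is not clean either. It adds onset of 4 mg to offset of the earlier treatment, shrinks with carry-over, and uses only subjects who reach Visit 7. Against the arms not on 4 mg it also mixes two doses. It does not measure duration of response, which is the stated purpose of the period. For these reasons it should supplement the existing summaries, not replace them.

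Three stronger readings are tempting, and the documents do not support them:

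- A reader might infer that carry-over is counted as drug effect. Placebo subjects have no earlier prosaptide to carry over. In the active arms, carry-over makes the change after stopping smaller, so it hides a drug effect.
- A reader might infer that a lasting drug effect will be read as placebo response. The wording in section 3.1 is open to other readings, and section 6.1.5 tracks the return to baseline in prosaptide successes, which treats a lasting effect as persistence of response.
- A reader might infer that the secondary Week 1 objective draws on crossover data. Sections 2.2, 2.4 and 6.1.5 keep it on the randomised comparison with placebo.

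**Conclusion.** The point holds as a modest one. Section 6.1 allows an uncontrolled before-after change to be read as a crossover treatment effect, although a randomised comparison that removes shared time and expectation effects is available.

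The error depends on a drift that the protocol does not give: none beyond 5% at zero drift, about 22% at 0.05 and about 53% at 0.085, with 70 subjects and an assumed SD of 0.35. The between-arm test holds about 5% only in so far as the drift is common to the arms. The 98% at a drift of 0.17 requires the whole placebo response used for sizing to recur within these two weeks. Nothing in the protocol supports that, so it should not be quoted as an expected rate.

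**What to change.** In section 6.1:

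- Label the within-group Visit 7 to Visit 8 changes and the duration-of-effect summary as descriptive only, and keep both.
- Base any statement about a crossover treatment effect on the between-arm difference in change, with a 95% CI. Use the change from Week 6 to Weeks 7 and 8 for the diary scores, and from Visit 7 to Visit 8 for the visit-based measures. The chief contrast is placebo-to-4 mg versus 4 mg-to-placebo.
- State that this contrast combines onset and offset, is reduced by carry-over, and includes only subjects who reach Visit 7.

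In section 3.1, qualify the sentence on placebo response and early pain response by saying that the placebo-to-4 mg change has no concurrent placebo control.

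The cost is a few sentences and no new data. The price in the analysis is a standard error larger by a factor of √2 than for a within-arm change, and an estimand that combines starting and stopping treatment.
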